### Data analysis

We will use multivariable linear regression analysis to evaluate the effects of medication adherence of comorbid patients with type 2 diabetes and depression on the decline of renal function. We will consider other potential confounding factors including smoking, hypertension, hyperlipidemia, and HbA1c. The risk of decline of renal function will be estimated for four groups by adherence (+/−) and depression (+/−) by odds ratio and 95 % confidence interval.

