**Methods/Design:**

In this multicenter cohort study, 550 patients with type 2 diabetes aged 20 years and older will be recruited at 20 outpatient clinics in general medicine and psychiatry. We will measure depression (Patient Health Questionnaire), medication adherence (medication possession ratio, Morisky Medication Adherence Scale, and one-item hypoglycemic medication adherence scale), and renal function (urinary albumin-creatinine ratio and estimated glomerular filtration rate) at baseline and at the 12-month follow-up. The primary endpoint is decline of renal function at 12 months. The secondary endpoints include clinical variables, quality of life, and the attitude of professionals toward depression. We will perform multivariable linear regression analysis to evaluate the effects of medication adherence on the decline of renal function in comorbid patients with type 2 diabetes and depression.

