### Study endpoints

The primary outcome is the decline of renal function in four subtypes categorized according to depression and adherence (depression/adherence: +/−, +/+, −/+, −/−) at 12 months. The secondary outcomes include clinical variables, quality of life, and attitude of physicians toward depression. We assess physician attitudes to depression to confirm no effects of the attitudes on primary outcome in a sensitivity analysis. Previous systematic review suggests necessity for cohort studies to examine information on patients with multimorbidity across all ages and socioeconomic groups [16]. Although analyses of secondary outcomes will be underpowered, we include the analyses in the protocol for confirmation of the analysis of primary outcome and implication for the future studies.

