### Renal function

Renal function will be assessed on the basis of ACR and estimated glomerular filtration rate (eGFR) [17, 18], and the decline of renal function is defined as ACR ≥ 30 mg/g creatinine and eGFR < 60 mL⋅min^−1^⋅1.73 m^−2^.

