### Sample-size calculations

We calculated sample size as 550 patients (165 for the depression group and 385 for the non-depression group) having (1) a 30 % prevalence of depression, (2) 10 % difference in microalbuminuria rate (18 % in the depression group and 8 % in the non-depression group), and (3) an 88 % chance of detecting a true difference in microalbuminuria at the 5 % level of significance. Calculation was based on the chi-square test with continuity correction and we did not take into account of adherence since it might be an intermediate variable. The prevalence of depression in patients with diabetes was 20 % in previous studies [5, 6, 10, 11]; however, we estimated 30 % owing to the inclusion of patients from psychiatric clinics in our study. The prevalence of microalbuminuria was estimated by using the data of the Japanese Society of Nephrology [18] and those from a previous study [11].

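### The only regression named for the threshold-defined primary endpoint is linear, but the promised effect measure is the odds ratio, which that model does not give

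*Protocol article*

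**What the plan says.** The relevant statements are spread over four parts of the protocol article.

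- **Endpoint.** Study endpoints: "The primary outcome is the decline of renal function in four subtypes categorized according to depression and adherence", assessed at 12 months. The Renal function section fixes the term: "the decline of renal function is defined as ACR ≥ 30 mg/g creatinine and eGFR < 60". This is a threshold rule, so the result per patient is yes or no.
- **Model.** Data analysis: "We will use multivariable linear regression analysis to evaluate the effects of medication adherence" in comorbid patients, with decline of renal function as the outcome. The abstract repeats it: "We will perform multivariable linear regression analysis to evaluate the effects of medication adherence on the decline of renal function".
- **Adjustment.** The next sentence of Data analysis reads: "We will consider other potential confounding factors including smoking, hypertension, hyperlipidemia, and HbA1c".
- **Effect measure.** The last sentence of Data analysis says the risk of decline will be estimated for the four groups formed by adherence and depression, "by odds ratio and 95 % confidence interval".

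Table 1 lists ACR and eGFR at baseline and at one year. Sample-size calculations treats the renal outcome as a proportion, with "550 patients (165 for the depression group and 385 for the non-depression group" compared by a continuity-corrected chi-square test.

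**The concern.** Three elements have to fit together: a yes/no endpoint, a regression model and an effect measure. The endpoint and the effect measure fit each other, since an odds ratio is a natural summary for a yes/no outcome. The named model fits neither. Linear regression appears in both the abstract and Data analysis, so it does not look like an isolated slip, and no logistic or other odds-ratio model appears anywhere.

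What is at stake is which quantity counts as the primary result. As written, an analyst could fit a linear probability model and report risk differences, choose a continuous ACR or eGFR outcome for the linear model, or add a logistic model that the plan does not name. Each gives a different headline result. The text does not choose between them, so the choice could be made after the data are seen.

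**Working it through.** **1. Endpoint, model and effect measure side by side**

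| Element | Where stated | Type |
|---|---|---|
| Decline of renal function | Renal function | Yes/no, by cut-offs |
| Primary comparison | Study endpoints | Four depression/adherence groups at 12 months |
| Regression named | Abstract; Data analysis | Multivariable linear |
| Effect measure | Data analysis | Odds ratio, 95% CI |
| Sample-size test | Sample-size calculations | Two proportions, corrected chi-square |

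Only the regression is out of line with the rest.

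**2. The plan's own figure, reproduced**

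Inputs from Sample-size calculations: n1 = 165, n2 = 385, p1 = 0.18, p2 = 0.08, 5% level (two-sided assumed; the text does not say).

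- Pooled rate: (165 × 0.18 + 385 × 0.08)/550 = 60.5/550 = 0.11.
- SE under equal rates: √[0.11 × 0.89 × (1/165 + 1/385)] = 0.0291.
- SE under the assumed rates: √[0.18 × 0.82/165 + 0.08 × 0.92/385] = 0.0330.
- Continuity term: ½ × (1/165 + 1/385) = 0.0043.
- Power: Φ[(0.10 − 0.0043 − 1.96 × 0.0291)/0.0330] = Φ(1.17) = 87.9%.

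Exact enumeration of the corrected test gives 88.6%. The stated 88% reproduces, which confirms that the study was sized on a binary outcome.

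**3. What each model returns at those rates**

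These are microalbuminuria rates by depression status, used only to show the scales.

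- Linear model coefficient: 0.18 − 0.08 = 0.10.
- Odds ratio: (0.18/0.82)/(0.08/0.92) = 2.52.

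Fitting both models to counts near these rates (30/165 vs 31/385):

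- Ordinary least squares: slope 0.101 (95% CI 0.044 to 0.158). Its exponential, 1.11, is not an odds ratio.
- Logistic regression: odds ratio 2.54 (95% CI 1.48 to 4.35).

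With covariates, a linear coefficient does not convert to a single odds ratio. A coefficient of 0.10 means 2.52 when the starting risk is 0.08. When the starting risk is 0.18, the risk rises to 0.28 and the odds ratio is (0.28/0.72)/(0.18/0.82) = 1.77.

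**4. Unequal variance, as a side issue**

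- Outcome variances: 0.18 × 0.82 = 0.148 and 0.08 × 0.92 = 0.074.
- Residual variance in the ordinary linear model: (165 × 0.1476 + 385 × 0.0736)/548 = 0.0962.
- Ordinary SE: √[0.0962 × (1/165 + 1/385)] = 0.0289, against 0.0330 with unequal variances, so about 12% too small.
- Ratio of the difference to its SE: 0.10/0.0289 = 3.5 against 0.10/0.0330 = 3.0, with the same conclusion.

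**The case against.** The strongest reply is that Data analysis describes two separate analyses. One sentence applies linear regression to adherence effects in comorbid patients; another gives odds ratios for the four groups. Nothing says the odds ratios come from the linear model, and a journal article may leave the name of the second model to the fuller plan. This reading is possible, but it does not remove the mismatch. The linear sentence uses the very term that the Renal function section defines by cut-offs, and no continuous version of it is designated.

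Several stronger readings are tempting, and the documents do not support them:

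- **That no continuous renal variable exists.** ACR and eGFR are listed for both visits. The accurate statement is that neither is named as the linear model's outcome.
- **That the four-group odds ratios would be crude.** The confounder sentence stands between the two analyses and is not limited to the first, and the Discussion says the major confounders will be controlled. Adjustment is signalled; what is missing is a model that delivers it on the odds-ratio scale.
- **That a linear model here is invalid.** A linear probability model is legitimate and a risk difference is a sound measure. The standard error is only about 12% too small in the illustration, robust standard errors cure that, and in a two-group comparison equal risks imply equal variances, so the false-positive rate is not inflated by this route.
- **That 0.10 against 2.52 shows bias.** These are one contrast on two scales. The rates are for microalbuminuria by depression status, neither for the combined ACR and eGFR endpoint nor for an adherence effect.

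**Conclusion.** The point holds as a contradiction within the text: the named model fits neither the threshold-defined endpoint nor the promised effect measure. It is a wrong statement and not an omitted detail, because a specific model is named, in two places.

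Its size is best described as ambiguity about the primary result. The article gives no event rates for the combined endpoint, so no numerical bias can be calculated. The conclusion rests on reading decline of renal function in Data analysis with the meaning that the Renal function section gives it; no other definition is offered. The sample size and power were already based on two proportions and are not affected by this point.

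**What to change.** In the abstract and in Data analysis, name multivariable logistic regression for the binary endpoint. Enter the four-level depression/adherence factor and the listed confounders (smoking, hypertension, hyperlipidemia, HbA1c), and report adjusted odds ratios with 95% confidence intervals.

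Keep linear regression only if a continuous outcome is explicitly defined for it, for example 12-month eGFR or ACR adjusted for its baseline value, and say whether that analysis is secondary. Otherwise delete it.

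The cost is a change of wording in two places, best made before the 12-month data are analysed. No new data are needed and the sample size of 550 stays as it is.

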### Participants

All patients who meet inclusion criteria during the study period will be invited to participate in the study. Participants will be eligible for the study if they (1) are 20 years and older, (2) outpatients with type 2 diabetes receiving hypoglycemic medications, and (3) can complete a questionnaire in Japanese. Patients will be excluded if they (1) have cognitive impairment, (2) are pregnant, and (3) have severe disease of the adrenal glands, liver dysfunction, or severe renal impairment (serum creatinine ≥ 2.0 mg/dL).

Eligible patients will be approached by physicians at each site. After an explanation of the study, written informed consent will be obtained from each patient. Patients will be able to access research staff members who are not in charge of their treatment to withdraw from the study at any time.

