### Data collection

Data will be collected at routine clinic visits by coordinating staff at baseline and 12 months. The data include patients’ demographic variables (e.g., age, gender, and smoking status), body mass index, prescription, blood pressure, laboratory data (e.g., glucose level, HbA1c, total cholesterol, low- or high-density lipoprotein cholesterol, triglycerides, serum creatinine, and urinary albumin-creatinine ratio [ACR]), and diabetic complications. Table 1 shows the primary measures and timings for measurement.

**Table 1 Tab1:** Measures and timings for measurements

	Scale	Baseline	1 Year
Renal function	urinary albumin-creatinine ratio (ACR) estimated glomerular filtration rate (eGFR)	●	●
Depression	Patient Health Questionnaire (9-item): PHQ-9	●	●
Adherence	Medication Possession Ratio (MPR) Morisky Medication Adherence Scale (MMAS-8) Oral Hypoglycemic Agent (OHA) adherence	●	●
Quality of life	EuroQol	●	●

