## Discussion

To our knowledge, the present study will be the first study to examine how adherence to hypoglycemic medication relates to the decline of renal function in comorbid patients with type 2 diabetes and depression. Given the prevalence of diabetes and depression, the impact of the comorbidity of these diseases is increasingly important. We will use all standardized measures. Renal function is assessed by urinary ACR and eGFR. As an increase of ACR is observed earlier than a decrease of eGFR in CKD, our study design aids in the better understanding of renal function decline from the early phase in comorbid patients with type 2 diabetes and depression. Adherence is assessed by both objective (MPR) and subjective (MMAS-8 and OHA) measures. MMAS-8 measures general adherence to medication, whereas OHA specifically measures adherence to hypoglycemic medication. A wide range of outcomes, including clinical variables, quality of life, and attitude of professionals toward depression, are also assessed.

This study design has several limitations. First, the participants will be patients who regularly visit clinic, causing a risk of bias. This might limit the generalizability of the findings. Second, our study will not include all possible confounding factors related to diabetes, depression, hypoglycemic medication adherence, and decline of renal function; nevertheless, we plan to control the major potential confounding factors.

The results of the present study will have implications to practitioners in diabetes care, policy makers, and researchers for screening a group of patients at a high risk for diabetic nephropathy (i.e., comorbid patients with type 2 diabetes and depression plus poor adherence to hypoglycemic medication) and for the development of intervention strategies for the prevention and treatment of diabetic nephropathy.

In conclusion, the results of this protocol study will indicate the importance of depression in diabetic care through exploring (1) depression as a predictor of renal function decline, and (2) how adherence to hypoglycemic medication relates to depression and renal function decline. Our research will provide insights to all clinicians who encounter comorbid patients with diabetes and depression in dairy practice.

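### The named confounders omit age, gender and baseline renal function, so odds ratios for a 12-month threshold status may partly reflect disease already present at entry

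*Protocol article*

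**What the plan says.** The Data analysis section of the protocol article is the only place that names adjustment variables: "We will consider other potential confounding factors including smoking, hypertension, hyperlipidemia, and HbA1c". The effect measure follows in the same section: "The risk of decline of renal function will be estimated for four groups by adherence (+/−) and depression (+/−) by odds ratio", with a 95% confidence interval. The Discussion concedes that not every confounder is covered, but adds that "we plan to control the major potential confounding factors".

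The variables at issue are available. Data collection states: "Data will be collected at routine clinic visits by coordinating staff at baseline and 12 months". The items recorded include "demographic variables (e.g., age, gender, and smoking status", and Table 1 marks ACR and eGFR at both time points.

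The outcome is set under Renal function: "the decline of renal function is defined as ACR ≥ 30 mg/g creatinine and eGFR < 60". This definition makes no reference to the patient's own baseline value. Under Participants, the only renal exclusion is "severe renal impairment (serum creatinine ≥ 2.0 mg/dL".

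**The concern.** The first objective is whether depression predicts decline in renal function, and the second is how adherence relates to both. An analysis of decline has to separate what happened during follow-up from what was there at the start. Here the endpoint does not separate them, because it is a status at 12 months. The eligibility criteria do not either, because they remove only patients with high serum creatinine. That leaves the adjustment set, and the covariates named do not include baseline ACR or eGFR.

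Age and gender raise a lesser question of the same kind. Data collection lists them next to smoking status, yet only smoking reappears among the named confounders. Depression is also tied to recruitment source: the sample-size section raises its expected prevalence from 20% to 30% because psychiatric clinics take part. Different patient mixes by depression status are therefore plausible, though the document reports none.

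If these variables stay out of the primary model and are unbalanced between groups, the four-group odds ratios could show an association that is not decline, or hide one that is.

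**Working it through.** **1. The plan's own figure.** Inputs from Sample-size calculations: 165 and 385 patients, 18% versus 8%, 5% level (taken as two-sided), continuity-corrected chi-square.

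- Pooled rate = (165 × 0.18 + 385 × 0.08)/550 = 60.5/550 = 0.11.
- Standard error under the null = √[0.11 × 0.89 × (1/165 + 1/385)] = 0.0291.
- Standard error under the alternative = √(0.18 × 0.82/165 + 0.08 × 0.92/385) = 0.0330.
- Continuity term = ½(1/165 + 1/385) = 0.0043.
- Power = Φ[(0.10 − 0.0043 − 1.96 × 0.0291)/0.0330] = 87.9%.

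Exact enumeration gives 88.6%. Solving for 88% power gives 166 depressed patients and about 553 in total. The stated 550 and 88% are reproduced, and the present point does not affect them. The planning odds ratio is (0.18/0.82)/(0.08/0.92) = 2.52.

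**2. Can a patient with existing disease count as declined?** Set the Participants and Renal function sections side by side. Someone with ACR of at least 30 mg/g and eGFR below 60 at entry, but serum creatinine below 2.0 mg/dL, is eligible. If nothing changes, that person meets the outcome at 12 months. So yes.

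**3. What that could do to the odds ratio.** The document gives no baseline renal figures by depression group, so every input here is an assumption: 12-month outcome risk of 3% without baseline impairment and 30% to 80% with it, and no effect of depression once baseline impairment is known (conditional odds ratio 1). The outcome risk in a group with baseline prevalence p is q = p × r₁ + (1 − p) × 0.03, where r₁ is the risk with baseline impairment. The unadjusted odds ratio is [q₁/(1 − q₁)]/[q₀/(1 − q₀)], with subscript 1 for depressed patients.

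| Baseline impairment, depressed vs non-depressed (assumed) | Unadjusted odds ratio, r₁ = 30% | r₁ = 80% |
|---|---|---|
| 10% vs 10% | 1.00 | 1.00 |
| 15% vs 10% | 1.25 | 1.42 |
| 20% vs 10% | 1.52 | 1.88 |
| 18% vs 8% | 1.57 | 2.01 |
| 10% vs 15% | 0.80 | 0.70 |
| 10% vs 20% | 0.66 | 0.53 |

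For 18% vs 8% at r₁ = 30%: q₁ = 0.18 × 0.30 + 0.82 × 0.03 = 0.0786 and q₀ = 0.08 × 0.30 + 0.92 × 0.03 = 0.0516. The odds ratio is 0.0853/0.0544 = 1.57. At r₁ = 80%: q₁ = 0.1686, q₀ = 0.0916, odds ratio 2.01. The 18% and 8% are the plan's microalbuminuria rates, carried over to baseline impairment by assumption.

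**4. Age.** A rough bias factor is exp[−(gap/10) × ln(odds ratio per decade)] when depressed patients are younger, and its inverse when they are older. Neither input is in the document. An assumed gap of 3 years at 1.5 per decade gives 0.885; 10 years at 2.0 per decade gives 0.50. Applied to 2.52 in both directions, the extremes are 1.26 and 5.04. A range that wide shows only that imbalance could matter; it is not evidence that it does.

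**5. Events available.** The 60.5 expected events in step 1 are for microalbuminuria. The defined outcome requires both ACR and eGFR criteria, and the document gives no rate for it.

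**The case against.** The strongest case against is that the list is illustrative. It is introduced as examples to consider, and the Discussion promises control of the major confounders. Nothing says that age, gender or baseline renal function will be left out. This stands: a reader might infer that the model will adjust for the four named variables only, or that the odds ratios are in fact confounded, and the document supports neither reading. Confounding needs imbalance between the groups, and no group-level figures are given. Nor does the article state how far age and gender determine eGFR or ACR.

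A second objection is that a short journal article may leave the full covariate list to an analysis plan. That would dispose of a complaint about missing detail alone. But this article chose to name covariates, and it paired them with an endpoint that cannot tell existing disease from decline. Under that endpoint the baseline value of the outcome is part of what makes the stated question answerable. An open list of variables to consider also leaves the primary adjustment set to be chosen after the data are seen.

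A third objection is that covariate adjustment is not the only remedy: the outcome could be redefined, or the analysis restricted to patients free of it at entry. This is also fair. Either would deal with existing disease, but restriction loses patients and neither deals with age and gender.

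**Conclusion.** The point holds in a limited form. Age, gender and baseline ACR and eGFR are collected but not named as adjustment variables. Because decline is a 12-month threshold status and entry screens out only high serum creatinine, odds ratios not adjusted for baseline renal function may reflect disease present at entry. They may also be confounded by age and gender. The baseline renal function part is the stronger of the two, because it follows from the article's own endpoint and eligibility rules.

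Size and direction cannot be derived from the document. On the assumed inputs shown, an imbalance in baseline impairment alone moves a null depression effect to anywhere from 0.53 to 2.01, and with no imbalance there is no bias. This is a worthwhile and nearly free improvement to the plan; it does not show that the results will be biased.

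**What to change.** State in the Data analysis section that the primary adjustment set includes age, gender, baseline log ACR and baseline eGFR, each as a single term, in addition to smoking, hypertension, hyperlipidemia and HbA1c. Report the depression and adherence estimates before and after this adjustment, so that readers can see how much of any association was present at entry.

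The cost is a sentence or two and no new data. The small downside is four more parameters. The figure of about 60 events should not be used to judge whether the model can carry them, since it applies to microalbuminuria. The expected or observed count for the combined ACR-and-eGFR outcome should be set against the model size before the covariate set is made final.
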